### Qualitative data analysis

All the interviews will be voice-recorded and transcribed verbatim. Transcripts will be imported to qualitative analysis software (NVivo) for data management and analysis. Framework analysis will be used to explore different cross-sectional descriptive data to capture different aspects of young people’s experience [19]. The researcher will read and re-read the data to familiarise herself with the initial emerging ideas. Codes then will be generated in a systematic fashion across the entire dataset and data will be assigned to the themes formed by the coding exercise. The researcher will then summarise and synthesise the coded data and refine the initial themes whilst identifying the associations and patterns, if any, between the themes. The researcher will then provide interpretation for the refined themes and seek for wider applications of the themes [19].

### Intention-to-treat analysis and imputation

We will carry out an intention-to-treat analysis. As a result, all patients randomised to participate in the trial will be evaluated in the final analysis even if they did not finish the trial or had the data uncompleted. Any missing data will be imputed using multiple imputation procedures. Missing data will be then replaced with a probable value based on other available variables in the data [20].

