#### Inclusion criteria

The eligibility criteria for inclusion in the trial will be:Aged from 10 to 14 years old and attending the Universidade do Estado do Rio de Janeiro (UERJ) Orthodontics Clinic at the peak of the pubertal spurt assessed using vertebral analysisFeatures of a class II, division 1 malocclusion with a convex profile and minimum overjet of 6 mm in permanent dentition, without missing teethParental informed consent

For the administering of self-reported questionnaires and semi-structured interviews, the participants will be recruited after they have completed the treatment. The intention will be to speak to all the young people who took part in the trial in the hope of achieving the theoretical data saturation point. A researcher with experience in conducting qualitative research will get in touch with young people via telephone. The researcher will explain the purpose of the interviews to the young people and invite them to take part in the study. The young people will be given at least 48 h to consider their decision and the researcher will call back to confirm the decision.

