### Analysis

#### Sample size

The primary outcome measure is the difference between the post- and pre-treatment position of the lower incisor edge calculated in millimeters. A 2-mm difference in primary outcome between groups is considered to be clinically significant. This value was obtained based on the clinical judgment of 18 dental professors, senior and junior lecturers, and post-graduate students via interviewing. The standard deviation of such difference was reported in the academic literature to be 1.65 [15]. Allowing for 5% type 1 error, 90% power and equal size allocation among groups, 32 subjects will be required. Considering a 20% attrition rate the total number of recruitment will be 40, with 20 in each group. This calculation was done using online open source software developed by Harvard University [16].

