#### Administrating self-reported questionnaire about patient discomfort

A 5-point Likert scale will be used to access patient discomfort. Measurements of discomfort will be made at the end of treatment, where a score of 1 indicates ‘no pain’ and a score of 5 ‘severe pain’. A mean score will be calculated for each group and compared to each other using paired Student’s *t* test.

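### Recruiting for the discomfort questionnaire only after completed treatment conflicts with the promise to evaluate every randomised child

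*Protocol article*

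**What the plan says.** All statements are in the protocol article.

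- **Intention-to-treat analysis and imputation:** "all patients randomised to participate in the trial will be evaluated in the final analysis even if they did not finish the trial". The section continues: "Any missing data will be imputed using multiple imputation procedures". The sentence after that reads: "Missing data will be then replaced with a probable value based on other available variables in the data".
- **Inclusion criteria**, on the questionnaires and interviews: "the participants will be recruited after they have completed the treatment". The same paragraph states a wider aim: "The intention will be to speak to all the young people who took part in the trial". A researcher telephones the young people, invites them, allows at least 48 hours and calls back for the decision.
- **Administrating self-reported questionnaire about patient discomfort:** "Measurements of discomfort will be made at the end of treatment". The scale runs from 1 to 5, and the two group means are tested against each other.
- **Sample size:** "Considering a 20% attrition rate the total number of recruitment will be 40", with 20 in each group.
- **Adverse events:** high levels of dental pain and extensive oral injuries are classed as serious, and patients may then leave the trial.

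**The concern.** The discomfort score is meant to compare the tolerability of the two appliances between randomised arms. That comparison keeps the protection of randomisation only if children are asked whether or not they finish. The Inclusion criteria section makes completed treatment the entry point for the questionnaire, so it selects on something that happens after randomisation and may depend on discomfort itself. The Adverse events section describes such a route, in which severe pain or injury may lead to leaving the trial. If the children with the worst experience are missing, and missing in different numbers or for different reasons in the two arms, the comparison describes those who tolerated their appliance and not all who were allocated to it.

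**Working it through.** **1. The plan's own numbers.** Inputs from Sample size: difference 2 mm, SD 1.65, type I error 5% (two-sided assumed), power 90%, equal allocation. The exact t-test power is 89.3% with 15 per arm and 91.3% with 16 per arm, so 16 × 2 = 32, as stated. For attrition, 32 / (1 − 0.20) = 40, or 20 per arm, also as stated. The planning figures are sound.

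**2. Children who could be left out.** Expected losses per arm are 0.20 × 20 = 4, or 8 of 40 in total. This is an upper figure for the present purpose, because some children counted as attrition might still be reached. Children who decline the separate telephone invitation would come on top.

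**3. The passages side by side.**
- Analysis set: all randomised patients, finished or not.
- Entry to the questionnaire: after completed treatment.
- Stated aim: to speak to everyone who took part.
- Timing of the score: end of treatment only.

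The second rule, taken literally, does not deliver the first or the third.

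**4. Whether imputation can close the gap.** Multiple imputation formally covers a missing discomfort score. But the scale is given once, at the end, and the In-treatment data section lists only photographs. Minor pain is recorded in the patient's notes as an adverse event, but that is not a score on this scale. A child who stops early therefore has no earlier discomfort score, and the imputation would lean on variables that do not measure discomfort.

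**5. How much the missing scores could matter.** Let p be the share missing in an arm. The mean over all randomised children is

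(1 − p) × (mean of those asked) + p × (mean of those not asked).

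The second mean can lie anywhere from 1 to 5, a span of 4. The arm mean is therefore open by p × 4, and the difference between arms by twice that when p is the same in both.

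| Missing per arm | p | Arm mean open by | Difference open by |
|---|---|---|---|
| 2 of 20 (assumed) | 0.10 | 0.4 | 0.8 |
| 4 of 20 (planned attrition) | 0.20 | 0.8 | 1.6 |

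These are widths of the possible range, not expected biases.

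**6. Direction.** Let d be the mean score of those not asked minus the mean of those asked. At p = 0.20, asking only completers understates an arm mean by 0.20 × d, for example 0.2 points if d = 1. The difference between arms is then biased by 0.20 × (d in one arm − d in the other). This is zero if d is equal in both arms and can take either sign otherwise. The document gives no information on d.

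**The case against.** The best defence is that the authors plainly want everyone. They intend to speak to all who took part, and a telephone call can reach a child who stopped early. The phrase about completing treatment may only mean the end of the appliance phase, for whatever reason it ended. The discomfort section says end of treatment without restricting it to completers, the imputation rule covers any missing data, and the figures with the participant flow and timeline are not available here. The outcome is also a secondary one.

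Much of this stands as a limit on the size of the point. It does not remove the conflict. The stated aim concerns speaking to the young people and is tied to reaching saturation in the interviews, whereas the recruitment sentence governs the questionnaire as well. If the aim is universal coverage, the recruitment rule should say so.

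Two stronger readings are tempting, and the document does not support either.

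- **Single imputation.** A reader might infer from the singular probable value that each gap is filled once and the t test is run as if all 40 values had been observed, which would overstate precision for the primary outcome. The sentence just before it names multiple imputation for any missing data, and nothing says that only one completed dataset is made or that pooling is omitted. The phrase is at most loose wording.
- **A known direction of bias.** A reader might infer that asking completers must flatter the less tolerable appliance. That depends on who stops in each arm and why, which the document does not tell us.

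**Conclusion.** The point holds for the discomfort comparison only. The rule for recruiting to the questionnaire conflicts with the intention-to-treat statement and with the authors' own aim of reaching all participants. Read literally, it could leave out up to about 4 of 20 children per arm, with no earlier score to impute from. The difference in mean discomfort would then be undetermined by up to 1.6 points on a 1 to 5 scale.

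This rests on the literal reading of the recruitment sentence and on the planned 20% attrition falling equally on both arms. That pain leads children to stop is a possibility raised by the safety section, not an established fact. The intention-to-treat promise for the primary outcome is not undone. The change is worth making because it is cheap, and scores not taken from early stoppers may not be recoverable later.

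**What to change.** In Inclusion criteria, separate the questionnaire from the interviews. Obtain agreement to the questionnaire at enrolment, and offer it to every randomised child when the appliance is removed, whenever and for whatever reason. Align the timing sentence in the discomfort section, so that the comparison follows the intention-to-treat statement. The interviews can keep their later invitation, provided it goes to all who took part, as intended.

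The cost is a small change to the consent wording and the handing out of an existing short form. Scores will then be taken after different lengths of wear, so time in treatment should be recorded with each. Children who never return for removal will still be missing, and imputation remains the fallback for them.

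As an optional editorial change, the probable-value sentence could speak of several plausible values with pooled results.

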### Patient’s timeline

The schedule of enrolment, interventions, and assessments can be seen in Fig. 10.

**Fig. 10 Fig10:**
[figure not shown]
Patient’s timeline. *Herbst appliance with skeletal anchorage. **Herbst appliance with dental anchorage

## Discussion

Orthopedic appliances have been used for many years to provide treatment for complex orthodontic problems. The Herbst appliance is a fixed functional appliance, which is becoming widely used worldwide. One of the side effects observed after its use is a vestibular inclination of the lower incisors. If this is not controlled the probability of relapse and other harms may be high.

This trial will only be the second trial of the Herbst appliance and the first to evaluate the potential of skeletal anchorage. As a result, the trial will generate much needed evidence for this rather complex form of orthodontic treatment. It will also serve as a model for other trials of orthodontic treatment techniques.

If we find that this new intervention is effective, the findings will change orthodontic practice and may also be relevant to other forms of treatment in which appliances are fixed to the bones of the jaws. However, if the bone anchoring is not effective, the trial will provide much needed information on the use of this comparatively new development. Finally, this will be the first trial that uses CBCT technology to measure tooth and skeletal bone change. This would be an important development and be a model for future research that uses this new method of image capture and analysis.

### Trial status

The trial has been recruiting since August 2015, with an expectation to finish the recruitment in August 2018.

### Safety reporting

#### Adverse events

In the case of adverse events, we will consider two types of adverse event:Non-serious adverse event: this will be any kind of adverse event resulting from the treatment. This will include minor pain, injuries, bruises or wounds to the oral tissues caused by some parts of the appliance, loosening or breakage of the appliance and failure of the mini-implants. In this case, the adverse event will be recorded in the patients’ notes. If any problem occurs to the appliance or mini-implant, it will be fixed and the participant will continue the treatment by the investigatorsSerious adverse event: this will be any kind of adverse event resulting from the appliances’ use which causes harms to the patient. This will include the swallowing of parts of the appliance, high levels of dental pain or temporomandibular joint, extensive problematic injuries, bruises or wounds to the oral tissues. In this case, urgent safety measures will be taken promptly by the team to ensure the safety and protection of the participants’ health. Patients may stop the trial if considered necessary (or they may continue if the Institutional Review Board consider that it is safe once the problems have resolved)

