**Fig. 3 Fig3:**
[figure not shown]
Herbst appliance with skeletal anchorage

#### Group 1

The Herbst appliance in group 1 will be the ‘cast splint’ type, made in cobalt-chromium (Herbst I set, Dentaurum, Ispringen, Germany). Group 1 will be anchored from the second molars to the first premolars in the upper arch and from the second molars to cuspids in the lower arch, following the Giessen University protocol [10].

At the first appointment, impressions from the upper and lower teeth will be taken with alginate (Orthoprint, Zhermack, Badia Polesine, Italy). Next, a construction-bite will be taken with wax. Then, the impressions and the registration will be sent to the laboratory for the construction of the Herbst appliance. The Herbst appliance will be placed on the second appointment.

#### Group 2

The Herbst appliance in group 2 will be the same as in group 1. However, its lower part will be anchored to mini-implants using 0.012" stainless-steel ligature wire (Morelli, Sorocaba, São Paulo, Brazil) from the mini-implants to a bracket soldered to the Herbst appliance on the buccal side of the cuspids.

Before placing the mini-implants, a cone-beam computed tomogram (CBCT) will be taken using Classic iCAT tomography (Image Sciences, Hatfield, PA, USA), to select the best site for insertion. We will then insert two self-tapping mini-implants (Neodent, Curitiba, Brazil), 2 mm in diameter × 10 mm in length, with attachments for the Herbst appliance telescopic tubes, between the roots of the cuspids and the first premolars or between the roots of the first and second premolars on each side, on the alveolar ridge through attached gingiva.

A lower rotation handpiece with torque control and a cone-shaped burr 1.3 mm in diameter (Neodent, Curitiba, Brazil) will be used to make a guide from the buccal to the lingual cortical bone in order to achieve bicortical anchorage. After the insertion of the mini-implants, new radiographs will be taken using the parallel technique to check if the mini-implants were inserted in the correct position.

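### The serious and non-serious adverse-event definitions differ in scope, are not cleanly separable and count only attributed events, so a severe mini-implant insertion harm (group 2 only) has no clear place in the serious class

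*Protocol article*

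**What the plan says.** In the Protocol article, Safety reporting, Adverse events, two types of event are considered.

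- **Non-serious.** "Non-serious adverse event: this will be any kind of adverse event resulting from the treatment". The examples are minor pain, injuries, bruises or wounds caused by parts of the appliance, and "loosening or breakage of the appliance and failure of the mini-implants". On recording: "In this case, the adverse event will be recorded in the patients’ notes".
- **Serious.** The definition opens with "this will be any kind of adverse event resulting from the appliances"; its full qualifying phrase is "resulting from the appliances’ use which causes harms to the patient". On examples: "This will include the swallowing of parts of the appliance, high levels of dental pain or temporomandibular joint, extensive problematic injuries, bruises or wounds", the last of these in the mouth. The urgent safety measures and the Institutional Review Board provision are written for this class only.

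The Group 2 text under Trial intervention describes a step that group 1 does not have. A burr is used "to make a guide from the buccal to the lingual cortical bone in order to achieve bicortical anchorage", and mini-implants are then inserted between tooth roots. The Blinding section states that the treating orthodontists cannot be blinded. The Baseline section under Data collection describes a Case Report Form completed by the clinician.

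**The concern.** The two definitions should divide one set of events by seriousness. Instead they start from different sets: the treatment in one case, use of the appliances in the other. The part of the first set that the second does not clearly reach is the insertion procedure, which only the experimental arm undergoes.

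Two further features make the rule weak. Causing harm is no threshold, since a small wound is also a harm. And both definitions admit an event only after someone has judged that the treatment or the appliance caused it, in a trial where the treating clinicians know the arm.

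At stake is the completeness and consistency of the safety record. The trial is motivated by reducing harm to the lower incisors, and its Discussion calls it the first to evaluate skeletal anchorage in this setting. Readers will want to know what the added procedure cost patients, and a severe event filed under the wrong class would also miss the safety steps attached to the serious class.

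**Working it through.** The plan gives no figure on this point, so the check sets the texts side by side.

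**Scope.**

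| | Non-serious | Serious |
|---|---|---|
| Attributed to | the treatment | use of the appliances |
| Further condition | none | causes harms |
| Mini-implants mentioned | yes, their failure | no |
| Stated action | notes; device problem fixed; treatment continues | urgent safety measures; Review Board provision |

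Mini-implant placement is part of group 2's treatment, so harm from it meets the non-serious definition. Whether it results from use of the appliances is doubtful for two reasons. Drilling and insertion are a preparatory step rather than use. The section also names the appliance and the mini-implant as separate items when it says what is done if either has a problem. Read literally, a severe insertion harm therefore meets the first definition and not the second.

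**Separation.** The non-serious definition has no upper limit: any event resulting from the treatment qualifies, which takes in everything the serious definition describes. Injuries, bruises and wounds stand in both example lists. What divides them is *minor* on one side and *extensive problematic* on the other. Neither term is defined, and in the first list it is unclear whether *minor* governs only pain or the whole series.

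**Attribution.** Let A be the events judged to result from treatment or appliance use, and B those judged not to. Both classes lie inside A. An event in B belongs to neither type and has no recording route in this section.

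**Exposure.** The sample size section plans 40 patients, 20 per group. Insertion is planned for 20 of 20 in group 2 and 0 of 20 in group 1, so the scope gap touches one arm only.

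**Recording.** Non-serious events are directed to the patients' notes. The section does not mention the Case Report Form for either class, although the trial has one.

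**The case against.** A reader might infer that insertion harm is left out of the safety rules altogether. The documents do not support that. The non-serious definition takes in any event resulting from the treatment, mini-implant failure is listed by name, and both example lists are open.

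A reader might also infer that the harm comparison is tilted towards skeletal anchorage. That is not shown either. The article plans no between-arm analysis of adverse events. The harms that are outcomes (gingival recession, root resorption and discomfort) are assessed in both groups without a causality judgement. Group 2 also has an extra listed event type and extra radiographs after insertion, which could raise its recorded count, and unblinded attribution can err in either direction.

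Three further objections deserve weight:

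- The serious list names wounds to oral tissues without a source, and the trial calls the whole group 2 device a Herbst appliance with skeletal anchorage. A drilling injury could be read into the serious class. This stands as a possible reading. It makes the classification ambiguous, but does not settle it.
- The lists are graded by severity, so a clinician has some working distinction. This also stands, but the grading is in undefined adjectives, while the definition itself rests on causing harm.
- An article may leave detailed seriousness criteria and forms to a full protocol. That would answer a complaint about missing detail. Here the rules are stated, and the stated rules do not fit together. Sending non-serious events to the notes does not, however, prove that they are kept off the Case Report Form.

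**Conclusion.** The point holds in a limited form. The two definitions differ in scope, both depend on attribution in a trial with unblinded clinicians, and causing harm does not separate them. Followed literally, a severe insertion harm in group 2 is captured only as non-serious or is ambiguously classified, and an event judged unrelated has no stated route into the record.

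The conclusion rests on reading use of the appliances as not including the drilling and placement of mini-implants. On the wider reading the ambiguity remains, but the gap narrows. The size cannot be put as a number of events, because the documents give no insertion risk and any rate would be an assumption. What can be stated is the exposure: all 20 planned group 2 patients and no group 1 patient. The primary outcome and the planned analyses are not affected. This is a worthwhile correction to a stated rule, not a threat to the trial's main result.

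**What to change.** Reconcile the two definitions as follows:

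1. Use one scope for both classes, worded to include mini-implant drilling and placement.
2. Record every untoward event from allocation to T2, whatever its judged cause, and hold the causality judgement in a separate field.
3. Separate serious from non-serious by a stated outcome-based criterion in place of the condition that harm is caused.
4. Enter events in both arms on the existing Case Report Form, and report patients with events by arm, with mini-implant failures listed separately.

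These changes concern definition, recording and reporting. The clinical response attached to each class is for the investigators and the Review Board to settle once the definitions agree.

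The cost is a protocol wording change, one Case Report Form page and slightly more recording work, with no extra visits. The article describes recruitment as still open, so events already written in the notes could be transferred and reclassified under the revised definitions.
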